Therefore, the SITLESS project aims to determine whether ERS can be enhanced by SMSs to reduce SB, increase PA and improve health, quality of life and function in the long term (22 months), as well as psychosocial outcomes in community-dwelling older European citizens from four countries, within a three-armed pragmatic randomised controlled trial (RCT), compared with ERS alone and also with general recommendations about PA. SITLESS will also collect health economics’ related outcomes, data on healthcare systems and community costs to perform cost-effectiveness analyses. SITLESS has the purpose to support policy-makers in deciding how or whether ERS should be further implemented or restructured in order to increase its adherence, impact and cost-effectiveness.

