### Sample size

A sample size of 1338 participants (randomised to one of three groups of 446 participants) will be needed to detect a moderate effect size of 30 daily counts per minute (CPM) in a two-sided test, at a power of 80% and an α of 0.05, a common standard deviation of 139 of the mean and a 24% dropout rate. A change of 30 CPM is considered a measurable moderate effect size in this population, assessed with ActiGraph GT3X+, and 139 is the standard deviation for CPM found in the literature [37]. The present sample size allows estimation of overall efficacy.

Sample size computations were conducted with online software GRANMO (http://www.imim.es/ofertadeserveis/software-public/granmo/; last accessed on 21/7/2014).

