### Data and statistical analysis

The full analysis set will follow the intention-to-treat principle and will include all randomised participants for whom a baseline assessment is conducted, regardless of later temporary or permanent loss to follow-up, withdrawal or drop-out of the study.

The study hypothesis will be tested with mixed linear models with repeated measures, to assess changes in main outcomes (SB and CPM) over time (T0 to T3) and between-study arms. A diagonal matrix design will be considered for the within-participants covariance matrices (covariance structure for repeated measures factors). Fixed effects in the analyses will be treatment group and country (study site), the latter based on its relevance as proxy for intervention and cultural differences. Random effects may be considered for the ERS + SMS group and ERS group, to take into account within-study clustering. A diagonal matrix design will be considered for the between-participants covariance matrices (covariance structure for random factors). The between-participants correlations induced by randomisation by centre and the clustering of cohabiting individuals will be taken into account in the models. Further testing of the study hypotheses will be conducted through covariance analyses, including in the model relevant covariates (age, gender, BMI, SPPB level and frailty), and effect modifiers.

Secondary analyses will be conducted to explore changes over time in the relative efficacy of the interventions. Mixed linear models with repeated measures will be built to assess changes over time between intervention groups in main and secondary variables, at baseline (T0) and T1, T2 and T3. Interaction terms between treatment and time will be considered to test for differences over time between treatments.

A sensitivity analysis will be conducted, restricted to the ‘per protocol’ dataset, comprising all participants with no protocol violations and complete (e.g. no missing data) measurements for the primary variables for all study assessments (baseline, end of treatment, first follow-up, second follow-up). A second sensitivity analyses will be conducted for any primary variable with a substantial number of missing values (higher than 5%), imputing missing data by the ‘last observation carried forward’ method.

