No subgroup analyses are planned in advance. Any subgroup analysis conducted will be treated with caution and output will be treated as exploratory rather than definitive. Missing data will be imputed through a multiple imputation approach, imputing missing values with the corresponding average values from the set of participants in the control group in the same country as the participant, matched for age, gender, baseline PA and baseline SPPB score.

Two-sided tests of statistical significance will be used in all statistical analyses. Estimates of the size of treatment effects will be presented together with confidence intervals, in addition to significance tests. Significance levels will be set to a 5% level, applying the Bonferroni correction to adjust for type I error criteria. All analyses will be performed with SPSS version 20 or Stata version 12.

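### The planned Bonferroni correction is valid, but a step-down test (Holm, or Shaffer for three pairwise contrasts) gives more power at the same 5% family-wise error: a cheap improvement

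*Protocol article*

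**What the plan says.** Under Data and statistical analysis, the protocol article sets the multiplicity rule in one sentence: "Significance levels will be set to a 5% level, applying the Bonferroni correction to adjust for type I error criteria". It gives no family, no divisor and no step-down version. Just before that it promises: "Estimates of the size of treatment effects will be presented together with confidence intervals, in addition to significance tests".

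The mixed models are "to assess changes in main outcomes (SB and CPM) over time (T0 to T3) and between-study arms", so there are two main outcomes and three arms. The aim in the Background is to test ERS + SMS "compared with ERS alone and also with general recommendations about PA", which names two of the three possible pairs.

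The Sample size section works "in a two-sided test, at a power of 80% and an α of 0.05", for a difference of 30 CPM, with "a common standard deviation of 139 of the mean and a 24% dropout rate". It mentions no multiplicity adjustment.

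**The concern.** Single-step Bonferroni holds every test in a family of m at 0.05/m, whatever the other tests show. Two facts go unused.

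- Once the smallest p-value is significant at 0.05/m, only m − 1 hypotheses can still be true, so the next may be tested at 0.05/(m − 1), and so on. This is Holm, and it is valid for any family and any correlation.
- With three arms and all three pairwise contrasts, if one pair of means differs, at most one of the other two equalities can be true. So after one rejection at 0.05/3, the other two may each be tested at 0.05. This is Shaffer.

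At stake is power on the contrasts the trial was built for. The aim compares ERS + SMS with both other arms. A full positive answer on both needs two rejections, and there single-step Bonferroni costs more than it does for a first rejection. The same data could leave ERS + SMS versus ERS non-significant when an equally strict procedure would reject.

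**Working it through.** **Inputs.** From Sample size: difference 30 CPM, SD 139, two-sided α 0.05, power 80%, dropout 24%, 446 per arm. From the Background and the analysis section: three arms, two named contrasts, two main outcomes.

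**The article's own figure.** n = 2(z₀.₉₇₅ + z₀.₈₀)² σ²/δ² = 2(1.960 + 0.842)² × 139²/30² = 337 per arm. Dividing by 0.76 gives 444 per arm, or 1332 in total; a t-test version gives 338, then 445. The stated 446 and 1338 are reproduced closely, at unadjusted α.

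**Power of one 30-CPM contrast.** Evaluable per arm: 446 × 0.76 = 339. The standard error of a difference is 139√(2/339) = 10.68, and 30/10.68 = 2.81.

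- Unadjusted: Φ(2.81 − 1.960) = 80.2%
- Bonferroni over 2 tests: Φ(2.81 − 2.241) = 71.5%
- Bonferroni over 3 tests: Φ(2.81 − 2.394) = 66.1%
- Bonferroni over 6 tests: Φ(2.81 − 2.638) = 56.8%

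**Step-down comparison.** Simulation of three independent arm means (SD 139, 339 per arm, 400,000 replicates). Ordered p-value thresholds for three tests are 0.05/3 throughout (Bonferroni); 0.05/3, 0.05/2, 0.05 (Holm); and 0.05/3, 0.05, 0.05 (Shaffer). Means are listed as control/ERS/ERS + SMS. The three patterns are assumptions, because the article does not say how the arms are expected to be ordered.

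Power for ERS + SMS to beat both other arms:

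| Means | 3 contrasts: Bonferroni / Holm / Shaffer | 2 SMS contrasts only: Bonferroni / Holm |
|---|---|---|
| 0/0/30 | 51 / 57 / 66% | 58 / 68% |
| 0/30/60 | 66 / 79 / 80% | 72 / 80% |
| 0/15/30 | 15 / 19 / 26% | 19 / 27% |

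Power per single contrast, family of three:

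| Means | Contrast | Bonferroni / Holm / Shaffer |
|---|---|---|
| 0/0/30 | each 30-CPM contrast | 66.1 / 69.4 / 73.9% |
| 0/30/60 | each 30-CPM contrast | 66.1 / 79.0 / 80.2% |
| 0/15/30 | the 30-CPM contrast | 65.9 / 66.8 / 67.8% |
| 0/15/30 | each 15-CPM contrast | 16.1 / 20.2 / 26.6% |

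The 60-CPM contrast in 0/30/60 stays at 99.9% under all three methods, so it has nothing to gain.

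Power to reject at least one hypothesis is identical under the three methods, because the first threshold is the same: 81.3%, 99.9% and 68.9% for the three patterns.

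**Error control.** Under the global null the family-wise error is 4.4% for all three methods. With one true null and the third arm different, Shaffer's false-rejection rate is 4.9% at 0/0/30 and 5.0% at 0/0/100.

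**If both outcomes share one family of six.** Bonferroni gives 56.8% for a 30-CPM contrast. Holm adds from about 1.4 points (second outcome null) to about 17 points (0/30/60 on both outcomes).

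**The case against.** The strongest reply is that nothing here is wrong. Bonferroni controls the error it is meant to control, and it has simple simultaneous intervals that agree with its tests. The article promises intervals, so a trialist may prefer that agreement. This stands. It makes the point an efficiency gain with a price, and a reader who inferred that the power is given up for nothing would go too far. With ordinary 95% intervals printed beside Shaffer decisions at 0/0/30, about 10% of simulated trials show an interval that excludes zero where the test does not reject.

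Second, the family is not stated. If it holds only the two SMS contrasts, Shaffer adds nothing to Holm. If both outcomes are pooled, Shaffer's three-test thresholds do not apply. This also stands, and it is why Holm is the default below. A reader might infer a general gain of 8 to 15 points. The article does not support that: Holm gains only 3 points per contrast at 0/0/30, the 30-CPM contrast gains 1 to 2 points at 0/15/30, and 0/30/60 assumes a 60-CPM difference from control, twice the planned effect.

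Third, if success required both SMS contrasts, each could be tested at 0.05 with no adjustment, with 69% power to win both at 0/0/30 against 66% for Shaffer. This is true, but the article states no such success rule and chooses a correction instead. The power to win both is therefore one relevant measure, not the trial's declared criterion.

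**Conclusion.** The point holds as a cheap improvement. For any family, Holm rejects at least what the planned Bonferroni correction rejects at the same strong 5% family-wise error, and Shaffer does better again for three pairwise contrasts of one outcome.

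On the article's inputs and the three assumed patterns of means, the gain in power to win both SMS contrasts runs from about 5 points (Holm over three contrasts, 0/15/30) to about 15 points (Shaffer, 0/0/30). Per single contrast in a family of three it runs from about 1 to 14 points, leaving aside the 60-CPM contrast already at 99.9%. It is zero for rejecting at least one hypothesis. These sizes rest on the assumed family, the assumed means, independent arm means and no allowance for clustering.

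Two stronger readings are not supported. The Bonferroni choice does not invalidate the analysis. Nor does a step-down test cure the separate mismatch that the trial was sized at unadjusted 0.05: at 0/0/30 Shaffer reaches 74% per contrast, still short of the planned 80%. Only the well-separated 0/30/60 pattern gets back to 80%.

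**What to change.** In Data and statistical analysis, replace the Bonferroni correction with Holm's step-down procedure at a family-wise 5% for whatever family is tested. If the family is the three pairwise arm contrasts of one outcome, name Shaffer instead: smallest p-value at 0.05/3 and, if that is significant, the other two at 0.05 each.

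Add a sentence saying whether the reported confidence intervals are unadjusted 95% or Bonferroni-adjusted, and that they may sometimes disagree with the step-down decisions.

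The cost is one or two sentences, with no extra participants or data. The procedures only compare ordered p-values with fixed thresholds, so the named software is no obstacle. The one real loss is the simple match between tests and simultaneous intervals. Trial status reports that no participant had completed the intervention at submission, so at that point the change could be made before any outcome comparison existed.

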## Discussion

This study provides a protocol for a multicentre pragmatic RCT to assess the effectiveness of existing ERS enhanced by SMSs to reduce SB, increase PA and improve health, quality of life, function and psychosocial outcomes in the long term (22 months) in older adults included in four European countries.

Currently, numerous RCTs have assessed the effects of PA-based interventions to improve health outcomes [21]. However, interventions aimed at reducing SB in older adults have only begun to emerge. There is growing evidence on how to promote healthier habits through SMSs based on behavioural interventions, but the integration of this knowledge into one complex and pragmatic RCT is a novel approach, as well as the expected impact in the long term. The foundation of this study is the existing ERS, which are implemented across Europe, but the adherence of professionals and older adults to ERS appears to be relatively poor. Therefore, SITLESS aims to impact health policy-makers with evidence-based knowledge to improve existing ERS by making them more effective.

Several national and international public health guidelines explicitly recommend that older adults should reduce their sedentary time and break prolonged periods of sitting to promote healthy ageing and wellbeing [62]. However, to date, few studies have investigated determinants of sitting and barriers and facilitators to change SB in older adults [63, 64]. Studies have reported determinants, barriers and facilitators specific to sitting that are different from those for PA. This might be due to the unique nature of SB, which occurs continuously during the day, compared to finite and set periods of PA or exercise occurring during the week. This suggests that interventions to reduce SB need to be specifically integrated into daily life.

When designing interventions to reduce SB and increase PA levels, rather than solely focusing on activities of at least moderate intensity, there is emerging evidence that replacing sitting time with standing or light PA may also provide substantial public health benefits [10, 65]. Some researchers had recognised that many older adults find it difficult to meet the PA guidelines of ≥150 min of moderate PA per week [66]. Therefore, a theoretic advantage of the SITLESS study is that promoting light PA may maximise the likelihood of people increasing their volume of PA along the continuum to a higher PA level [67].

Older adults are often unaware of exactly how long, where, when and why they sit [64]. Comparisons between self-reported and objective measures of SB have shown that older adults underestimate the time they spend sitting [16]. In the SITLESS trial, a combination of self-report and objective measures will be used. Moreover, the intervention itself pretends rising awareness on SB among participants.

The findings of this study will help inform the design of more effective interventions to reduce SB and increase PA levels, and hence improve health outcomes in the older adult population in the long term. The results of the present study may help to assist policy-makers of different European countries in deciding how or whether this intervention should be implemented widely or restructured.

### Study limitations

The SITLESS study faces an important challenge on how to standardise ERS and SMSs interventions across four European countries with different healthcare pathways. However, this is the first large RCT comparing ERS and ERS enhanced with SMSs to reduce SB in older adults, assessing many validated and objective outcome measures. SITLESS incorporates a process evaluation procedure throughout the trial providing greater confidence in conclusions about effectiveness.

### Trial status

This initial phase of this project commenced in May 2015. A feasibility study was performed from December 2015 until June 2016. The recruitment for the trial started in July 2016. At the time of submission of this protocol, less than 250 participants have been included in the study over a six-month recruitment period. To date, none of the participants have completed the intervention and no adverse events have been reported.

## Abbreviations

BCTs: Behaviour change techniques
CG: Control group
CPM: Counts per minute
ERS: Exercise referral schemes
HADS: Hospital Anxiety and Depression Scale
ICECAP-O: ICEpop CAPability measure for Older people
MET: Metabolic Equivalent Tasks
MRC: Medical Research Council
PA: Physical activity
PACE: Patient-centered Assessment and Counseling for Exercise
SB: Sedentary behaviour
SMSs: Self-management strategies
SPPB: Short Physical Performance Battery
WHO: World Health Organization
